## Abstract

**Introduction:**

Comorbidity between Substance Use Disorders and trauma/post-traumatic stress disorder (PTSD) is common, particularly within residential treatment services. Comorbidity is associated with poorer treatment retention and treatment outcomes. Integrated treatment approaches are increasingly recommended but are still under examined in residential treatment services. This study will implement and evaluate a novel model of trauma-informed care (TIC) in a youth (18–35 years) residential substance use treatment service.

**Methods and analysis:**

A single-armed, phase 1 implementation trial will be conducted in one residential treatment service. The model, co-developed with staff, incorporates: (i) workforce development in TIC through staff training and clinical supervision; adaptions to the service (ii) policies, procedures, and physical settings and (iii) treatment program adaptions (in delivery style and content) to be more trauma-informed; (iv) client screening and feedback for trauma and PTSD at service entry; and (v) the provision of support, referral and/or trauma-focused therapy to those with PTSD. Service outcomes will include adherence to the TIC model and client treatment completion. Client substance use and mental health measures will be collected at service entry, and 1-, 3-, 6- and 12-months follow up. Staff outcomes, including workplace satisfaction, burnout, and fatigue, as well as perceptions and confidence in delivering TIC will be collected at baseline, and at 3-, 6-, 12- and 18-months following training in the model. The sustainability of the delivery of the TIC model of care will be evaluated for 12 months using service and staff outcomes.

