## Procedure

The TIC model was developed over a 6-month period during 2020, and the initial implementation, including workforce training, occurred post development of the program. All clients will receive the residential TIC model as part of routine care. The evaluation phase of the TIC model will occur over a 12-month period once the initial implementation has been completed. Client outcomes will be assessed at baseline and 1-, 3-, 6- and 12-months follow up (till December 2022). Within 1 week of entry to the service, clients will receive verbal and written information of the trial by a research assistant and informed consent will be obtained. Only the data of clients who consent to participate in the project will be used to evaluate the effectiveness of the new model. All client participants will be followed up for intent-to-treat purposes, regardless of treatment completion. Reminders to complete the survey will be sent to participants via SMS and email. At 1-month and 3-month timepoints, the online survey and reminders will be sent as part of the service’s usual Outcome Measures procedure. At 6- and 12-months, research assistants will send out the surveys (as these time-points are not part of the services usual outcome measure procedures). Participants will be followed-up over the phone by research assistants not involved in treatment delivery or model design, if the survey is not completed within 1 week. Participants will be reimbursed $20 for completing each survey.

Staff outcomes will be collected at the TIC training, and again at 3-, 6-, 12- and 18-months post-training, via online surveys sent by email from research assistants not involved in treatment delivery or TIC model design. Staff will be sent reminders to complete the surveys by these research assistants and general reminders regarding the study by their team leader. Staff who are no longer working at the service will not be followed up.

The sustainability of the TIC model will be assessed for a 12-month period after the evaluation phase is complete, to determine if delivery of the TIC model is sustained once the formal evaluation ends. All clients who enter the service consent to their deidentified data being used for service evaluation purposes. During this time, the researchers will have minimal involvement in the running of the model. Service outcomes will be collected during this period (see below for outcomes).

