### Outcomes

#### Client outcomes

Client outcomes will be collected upon entry to the residential treatment service (baseline), and again at 1-, 3-, 6-, and 12-months later. See Table 3 for the list of measures, including measures that are collected as part of routine care and the additional measures completed for the evaluation. The primary outcome for the evaluation will be substance-related outcomes, assessed via the World Health Organization Alcohol, Smoking and Substance Involvement Screening Test (ASSIST) (67) and the Australian Treatment Outcomes Profile (ATOP) (68). Quality of life is assessed by the relevant items on the ATOP. PTSD upon treatment entry is measured using the Primary Care PTSD Screen for DSM-5 (64), a brief five-item measure of symptoms of PTSD over the last month. Those with a positive screen on the PC-PTSD (scored 3+), will be asked to complete the PTSD Checklist (PCL-5) (69), a 20-item measure of PTSD symptom severity, which will be the primary outcome for the CPT analyses. Secondary outcomes include measures of depression and anxiety using the Patient Health Questionnaire (PHQ-9) (70), (9-items) and the Generalized Anxiety Disorder Scale (GADS-7) (71) (7-items), respectively. Client satisfaction will be assessed via the five-item Patient Experience Questionnaire from the Improving Access to Psychological Therapies program (72). Open ended responses will also be included to collect feedback from the participants about their level of satisfaction with their treatment and to better inform treatment procedures.

**Table 3 tab3:** Study timelines and outcomes.

	Enrolment		Treatment		Follow up			
TIMEPOINT	*-t_1_*	*-t_2_*	*t1*	*t2*	6 weeks	3 months	6 months	12 months
*ENROLMENT:*								
*Staff informed consent*	X							
*Client informed consent*		X						
*Client eligibility*		X						
*INTERVENTIONS:*								
*Model development*	X							
*Staff training*		X						
*TIC trial*								
*Sustainability*					X	X	X	X
*Evaluation:*								
*Client measures*		X			X	X	X	X
Demographics		X						
WHO-assist		X				X	X	X
ATOP		X			X	X	X	X
PHQ-9^a^		X			X	X	X	X
GAD-7		X			X	X	X	X
PTSD screen*		X			X	X	X	X
PCL-5*		X			X	X	X	X
Distress tolerance scale		X			X	X	X	X
Resilience evaluation scale		X			X	X	X	X
PEQ					X	X	X	X
*Staff measures*	X				X	X	X	X

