#### Staff outcomes

Staff outcomes will be collected at the TIC training (baseline), and again at 3-, 6-, 12- and 18-months post-training. At each time point, the 59-item Knowledge, Principal Support, Self-efficacy, and Beliefs that Predict Commitment to Trauma-informed Care Survey (73) will be used to measure commitment to TIC (6 items), support for TIC (6 items), self-efficacy to implement TIC (7 items), beliefs about trauma in the workplace (10 items), and foundational knowledge about trauma (30 items). Staff perceptions of the five TIC values within an organization are also measured using the 10-item Trauma-Informed Climate Scale-10 (TICS-10) (74). Workplace satisfaction, burnout, and fatigue are assessed using the 30-item Professional Quality of Life Scale (V5, ProQOL) (75). An Organizational Self-Assessment of TIC (76) will also be measured at each time point to assess the extent to which the organization is implementing and progressing with a TIC model in three domains: organizational readiness for trauma-informed care change (6 items), competent trauma-informed organizational, clinical, and milieu practices (11 items), and consumer and family engagement (8 items). We will also measure staff turnover rates, and supervision attendance.

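### Sustainability is to be judged over 12 months partly on staff outcomes, but on the text's schedule the last staff survey falls no later than month 6 of that phase, and Table 3 gives a conflicting staff schedule

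*Protocol article*

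**What the plan says.** Abstract, Methods and analysis, on the sustainability evaluation: "The sustainability of the delivery of the TIC model of care will be evaluated for 12 months using service and staff outcomes". The same paragraph says that the staff measures "will be collected at baseline, and at 3-, 6-, 12- and 18-months following training in the model".

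Procedure, on the order of events: "the initial implementation, including workforce training, occurred post development of the program"; then "The evaluation phase of the TIC model will occur over a 12-month period once the initial implementation has been completed"; then "The sustainability of the TIC model will be assessed for a 12-month period after the evaluation phase is complete". For that last phase the Procedure names service outcomes as the data to be collected and does not mention staff outcomes.

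The staff schedule appears twice more in the text. Procedure: "Staff outcomes will be collected at the TIC training, and again at 3-, 6-, 12- and 18-months post-training". Staff outcomes: "Staff outcomes will be collected at the TIC training (baseline), and again at 3-, 6-, 12- and 18-months post-training". No text gives a later staff survey.

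Table 3 differs. Its row "Staff measures" is marked at the first enrolment point (-t1) and at 6 weeks, 3, 6 and 12 months. There is no 18-month column. The table's Sustainability row is marked in the same four follow-up columns, and the table does not say from what event those columns are counted.

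**The concern.** The abstract offers staff outcomes as one of two sources of evidence on whether the model lasts for 12 months after the formal evaluation. That is useful only if staff are measured well into those 12 months. At the end of the evaluation, supervision passes from a clinical psychologist on the project team to a team leader or manager in the service (Workforce development), and the researchers step back (Procedure). The staff battery includes commitment to trauma-informed care, organizational climate, burnout and an organizational self-assessment of how far the model is in place. If the surveys stop at or soon after the handover, these measures cannot show whether the change held.

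A reader must also be able to tell which staff schedule applies. The text and Table 3 cannot both be right as printed.

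**Working it through.** **Inputs**
- Staff training workshop: August 2020 (Workforce development).
- Staff surveys: months 0, 3, 6, 12 and 18 from training (Abstract, Procedure, Staff outcomes).
- Evaluation phase: 12 months, starting once initial implementation, which includes training, is complete (Procedure).
- Sustainability phase: the next 12 months (Procedure).
- Service-level outcomes: collected over approximately 24 months (Service-level outcomes).
- Client recruitment: 12 months (Sample size calculation). Client follow-up: 12 months, ending December 2022 (Procedure).

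**The plan's own figure.** Evaluation 12 + sustainability 12 = 24 months, which agrees with the stated period for service-level outcomes.

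**Position of the last staff survey.** Let L be the months from training to the start of evaluation. Training belongs to the implementation that comes first, so L ≥ 0. The sustainability phase runs from month 12 + L to month 24 + L after training. The last survey is at month 18, so it falls 18 − (12 + L) = 6 − L months into the phase.

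| L (months) | Sustainability phase (months after training) | Last survey, months into phase | Months of the phase after the last survey |
|---|---|---|---|
| 0 | 12 to 24 | 6 | 6 |
| 3 | 15 to 27 | 3 | 9 |
| 4 | 16 to 28 | 2 | 10 |
| 5 | 17 to 29 | 1 | 11 |
| 6 | 18 to 30 | 0 (at its start) | 12 |
| 8 | 20 to 32 | 2 months before it | 12 |

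**Calendar check.** August 2020 + 18 months = February 2022. The article gives no start date for the evaluation. If the 12-month recruitment period coincides with the evaluation phase (an assumption), then December 2022 − 12 months of follow-up = December 2021 for the last enrolment, and evaluation ran from about January to December 2021. L is then about 4 to 5, and the last survey falls at about month 1 to 2 of the sustainability phase. The group program workshops were spread across 2020 and 2021 (The group treatment program), which fits a start later than August 2020 but does not date it.

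**Text against Table 3**

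| Source | Staff time points |
|---|---|
| Text (three places) | training, 3, 6, 12, 18 months |
| Table 3 | -t1, 6 weeks, 3, 6, 12 months |

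The 18-month survey is only in the text, and the 6-week survey is only in the table. The table also puts the staff baseline at -t1 and staff training at -t2, whereas the text takes the baseline at the training.

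What the table implies for sustainability depends on its time origin:
- Counted from training, its last staff survey is at month 12, which is 12 − (12 + L) = −L: at or before the start of the phase.
- Counted from the start of the sustainability phase, its last staff survey is at month 12 of the phase, that is, month 24 + L after training.

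The second reading fits the Sustainability row, but then the text's schedule, which ends at month 18, is wrong. Neither reading makes the two agree.

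**The case against.** The strongest reply has four parts.

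**Table 3 marks sustainability and staff measures in the same columns.** A reader might infer from the table that no staff survey falls within the sustainability phase. The document does not support that. The inference requires counting the columns from training, which the table does not say, and its Sustainability row points the other way. This part stands: what can be said of the table is that its origin is unstated and that it conflicts with the text.

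**Aim (iii) concerns delivery of the model.** The current trial and the Procedure both frame it so. Delivery is covered by service outcomes over about 24 months, among them group attendance, time to first session and the share of group sessions run as planned. Data and analyses also promises frequencies of the outcomes in both phases. A reader might infer that aim (iii) cannot be answered. That is too strong, because the service part is intact. The abstract nevertheless names staff outcomes as evidence on sustainability, and that statement is what the text's schedule does not deliver in full.

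**Not every staff outcome is a survey.** Staff turnover and supervision attendance are listed under Staff outcomes and could come from records, and supervision continues after the evaluation. So it cannot be said that staff change goes wholly unobserved. The article does not give the collection period for these two measures, so this limits the point without removing it.

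**The timing is conditional.** With no start date for the evaluation, the month 1 to 2 figure is inferred. The upper limit of 6 months is not: it follows from the order and length of the phases alone.

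**Conclusion.** The abstract's statement is not met by the schedule in the text. Whatever the start date of the evaluation, at least the last 6 of the 12 sustainability months come after the final staff survey. With evaluation from January to December 2021 (assumed), it is about 10 to 11 of the 12. With evaluation starting more than 6 months after training, every staff survey precedes the phase. The 6-month bound rests only on training preceding the evaluation phase and on the two 12-month phases following one another.

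Two contradictions accompany this: the abstract names service and staff outcomes for sustainability while the Procedure names service outcomes only, and Table 3's staff row disagrees with all three statements of the staff schedule.

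The consequence is limited to survey-based staff measures (commitment, climate, burnout, organizational self-assessment) late in the phase. Service outcomes, and possibly turnover and supervision attendance, are still available, and the primary client analysis is not affected.

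**What to change.** 1. State the event from which the Table 3 follow-up columns are counted, for staff separately from clients if they differ. Reconcile the staff row, including the 6-week and 18-month points and the placing of the baseline relative to training, with the Abstract, Procedure and Staff outcomes.
2. Then choose one of two options:
   - Add one online staff survey at the end of the sustainability phase, which is month 24 + L and so 24 months or more after training, and name staff outcomes for this phase in the Procedure. The cost is one more survey for about 20 staff.
   - Restrict the abstract's sustainability statement to service outcomes and any staff measures taken from records, in line with the Procedure, and state that turnover and supervision attendance are collected through the phase if they are to be used. The cost is wording only, but the survey-based staff evidence late in the phase is given up.
3. Give the start and end dates of the evaluation and sustainability phases, so that the position of each staff survey can be read directly.

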**Ethics and dissemination:**

The study has received ethical approval by the University of Queensland (Approval number: 2020000949). The results will be disseminated through publication in a peer-reviewed scientific journal, presentations at scientific conferences, and distributed via a report and presentations to the partner organization.

**Clinical trial registration**: ACTRN12621000492853.

## Introduction

People with substance use disorders (SUDs) report disproportionately higher rates of lifetime trauma, which can both precede (1–5) and occur as a consequence of substance use (6). Research indicates up to 90% of those seeking help for SUDs report prior trauma (7, 8), which can precipitate post-traumatic stress disorder (PTSD); a psychiatric condition characterized by symptoms of intrusion, avoidance, negative mood and cognitions, hyperarousal, dissociation, and poor functioning (9). In particular, both childhood trauma and associated PTSD increase risk for early substance use, which is associated with greater severity and complexity of SUDs (10, 11). Comorbid SUD and PTSD is reported in 43–50% of individuals seeking SUD treatment (8, 12, 13), and is associated with poorer outcomes than a SUD or PTSD diagnosis alone. This includes a greater risk of disability, poorer physical and mental health (11, 14), and reduced treatment retention (15, 16). Current treatments for SUDs demonstrate limited long-term efficacy for reducing relapse and craving (17–19), and improving mental health outcome among people with comorbid SUD and PTSD (20). As a result, there are increasing calls for SUD treatment settings to offer trauma-informed and trauma-focused care (9, 21). The link between early trauma exposure, early substance use and greater severity of SUD, and the subsequent greater complexity of treatment needs underscores the importance of early intervention and trauma-informed care particularly for young people (22). Trauma-informed care (TIC) refers to service delivery that is grounded in an understanding of how trauma affects peoples’ lives, service needs, and service usage. Trauma-focused approaches provide integrated psychosocial treatment to address symptoms of SUD and PTSD concurrently.

Residential treatment is a common treatment approach for people with SUD and other mental health comorbidities. Services typically provide live-in treatment through structured programs and 24-h support in safe accommodation (23), although the nature and specifics of such services vary widely (24). Implementing TIC in residential treatment may reduce the risk of re-traumatization, enhance individual treatment outcomes, and improve staff confidence with managing trauma (25, 26). As residential treatment encompasses multiple systems of care, in which an individual is situated within a program that sits within a broader environment, integrating trauma informed models of care at both a service level and individual level may be particularly important.

### Trauma-informed care at a service level

An organizational approach to TIC assumes a history of trauma exposure in all clients, whereby there is a sensitivity to trauma at service system levels (27). Based on trauma theory and empirical evidence of trauma-informed practices to design service systems, common frameworks of trauma-informed care propose five essential values of TIC for staff and clients: safety (ensuring all staff and clients feel psychologically safe), trustworthiness (transparent operations and adequate follow through on promised services), choice (clients are given options wherever possible), and collaboration (partnering between clients and staff) through empowerment (reducing the power differentials between clients, staff and supervisors) (26, 28, 29). These guiding principles demonstrate distinct yet related benefits (30), and are measurable across an organization (30, 31). TIC has been implemented in psychiatric (32), justice (33, 34), medical (35), and child/youth welfare systems (36), for both outpatient and residential services. Benefits of TIC include greater staff satisfaction, retention, commitment, and performance (37). For clients, TIC is associated with reduced youth misconduct and increased feelings of safety in juvenile justice systems, reduced disciplinary events in schools, in addition to reduced aggressive patient incidents, restraints, and seclusions in inpatient psychiatric units [see (38), for a review]. However, much of this literature has evaluated outcomes using short follow-up periods and rarely has the sustainability of TIC models been evaluated post implementation (38).

In models of TIC developed for alcohol and drug use settings, trauma is addressed via: (i) routine screening for symptoms of PTSD in clients entering treatment, (ii) providing feedback to clients about their scores and offering appropriate support and/or treatment, (iii) ensuring the service environment is sensitive to trauma and its role in substance use, and (iv) training staff in TIC and providing them with appropriate supervision to identify and manage trauma-related reactions in clients (39). The delivery of integrated TIC substance use treatment can increase treatment retention in adults compared with standard treatment (40), and reduce PTSD symptoms in adolescents (41). However, limited research has implemented TIC in residential services for SUDs or examined sustainability of TIC models in substance use treatment settings.

### Trauma-informed treatment at an individual level

In addition to organizational practice approaches, the implementation of TIC may include individualized and group-based trauma-focused treatment (9). In outpatient settings, trauma-focused individual and group therapies are more effective at reducing both symptoms of PTSD and substance use, when compared to non-trauma therapies (see (42), for a review). One study also reported that trauma-focused therapy was not associated with any greater PTSD symptom exacerbation than relapse prevention (43), supporting the safety and tolerability of addressing trauma within treatment for SUDs.

Trauma-focused treatments typically use cognitive-behavioral principles to promote processing of the traumatic event and its meaning (44). One ‘gold-standard’ therapy for PTSD across several settings and populations is Cognitive Processing Therapy (CPT) (45–51). Two meta-analyses have demonstrated that CPT produces the greatest average effect sizes for improving PTSD outcomes when compared to psychotropic medication and other psychological treatments, including exposure-based interventions (52, 53). The treatment effects of CPT for PTSD have also been shown to be enduring 5 years after treatment (54). Despite this, there has been limited research examining integrated CPT for concurrent PTSD and SUD, with one study using a single case design in an outpatient setting (55, 56). Further exploration on how CPT could be integrated into the treatment of SUDs in residential settings may help to reduce comorbid symptoms of PTSD.

